### Subjects

#### Inclusion and exclusion criteria

Patients will be recruited from vascular, cardiology and nephrology outpatient clinics of 11 hospitals including two university hospitals. Patients are eligible for participation if they fulfill the criteria of resistant hypertension, use at least two AHDs for which DBS-analysis are available, are 18 years or older and are able to provide informed consent. Due to the large population of people orginating from Turkey in Rotterdam, the patient information leaflet is made available in both the Dutch and Turkish language.

Resistant hypertension is defined as having an office BP of > 140 mmHg (systolic) and/or 90 mmHg (diastolic) or, if available, a 24-h ambulatory blood pressure measurement (24-h ABPM) daytime BP of > 135 mmHg and/or 85 mmHg despite a medication regimen of AHDs in the maximal tolerable dose of at least three AHDs from different drug classes, including a diuretic, or at least four AHDs from different drug classes. In Table 1 the minimal drug dose needed at time of the inclusion and the lower limit of detection of each included drug are shown. DBS analysis includes the following AHDs and active metabolites: enalapril and enalaprilate, perindopril and perindoprilate, irbesartan, valsartan, losartan and losartan-carboxylic acid (losartan-CA), hydrochlorothiazide, bumetanide, spironolactone and canrenone, amlodipine, barnidipine, nifedipine, metoprolol and doxazosin [25, 26].

**Table 1 Tab1:** Overview antihypertensive drugs included in the RHYME-RCT trial

Antihypertensive drug [metabolite]	Minimal drug dose for inclusion (mg)	LLOD (μg/L) [25]
Amlodipine	5	17.1
Barnidipine	10	2.1
Bumetanide	1	4.0
Doxazosin	4	18.1
Enalapril	20	0.4
[Enalaprilat]	–	1.1
Hydrochlorothiazide	12.5	40.2
Irbesartan	150	7.7
Losartan	50	1.7
[Losartan-CA]	–	2.6
Metoprolol	50 CR or 25 mg two times daily (normal release)	0
Nifedipine	30	3.5
Perindopril	4	0.7
[Perindoprilat]	–	1.3
Spironolactone	12.5	5.2
[Canrenone]	–	26.8
Valsartan	80	21.3

*CA* carboxylic acid; *CR* controlled release, *LLOD* lower limit of detection

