#### Standard of care (SoC) alone

SoC includes visits at 3 (t3), 6 (t6), and 12 (t12) months follow-up, with preferably a 24-h ABPM, and otherwise an automated office blood pressure (AOBP) combined with DBS sampling. In the SoC arm the results on drug concentrations are not reported during the study and are only used for resarch purposes.

The results of the blood pressure measurements are available for all healthcare providers. If deemed necessary by the treating physician it is allowed to schedule extra appointments outside the research visits. Also, it is allowed to make changes to the AHD treatment during every visit, without restriction with regard to the choice or dose of drugs. These changes are registered at every visit. If a patient switched to AHDs that are not included in the TDM method, only blood pressure measurements are included in the analysis.

Patients are allowed to make life style changes during the trial. These life style changes can possibly influence the adherence outcome and is therefore taken into account in our power calculation.

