#### Secondary objectives

Secondary endpoints include the effect of the intervention on the proportion of patients adherent to AHDs and patients fulfilling the definition of RH over time including baseline (t0), t3, t6 and t12.

Furthermore, the number of required AHDs as well as the defined daily dose (DDD) is calculated at t0 and t12 in both arms to determine if there is a difference over time between the arms.

Lastly, the cost-utility of the intervention vs standard of care in resistant hypertension is determined.

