#### Statistical analysis

Continous variables with a normal distribution are described as mean value ± one standard deviation (SD), and otherwise as median value (25th–75th percentile). Normality is tested by the Shapiro–Wilk test. Categorical variables are described as numbers and percentages. Within group changes in percentage non-adherence and RH from t0 to t12 are evaluated by McNemar tests. We use a Chi^2^-test to study change-differences in non-adherence and RH between patients randomised to the intervention + SoC versus SoC alone.

The defined daily dose (DDD) is the assumed average maintenance dose of a drug used for its main indication in adults [36]. These averages are used to determine how many times the DDD for each individual drug is used. Subsequently, the averages of these DDDs are calculated for t0 and t12 for individual patients.

Differences in blood pressure and DDDs over time within the same arm are tested by means of a paired sample t-test and differences between patients randomised to the intervention + SoC versus SoC alone with a independent samples t-test.

We will perform an intention-to-treat analysis, including all randomised patients, as well as a per-protocol analysis, including the patients with available measurements at t0 and t12, and one of t3 and t6.

Data from the questionnaires are used for the cost-effectiveness and cost-utility analysis of the intervention. A cost-utility analysis will be performed with quality adjusted life years (QALY) for a lifelong period. The QALYs will be calculated based on the EQ-5D-5L summary score. Cost-effectiveness from a healthcare perspective will be calculated for a 1-year period using the number of patients fulfilling the definition of resistant hypertension after 12 months (the primary outcome measure).

All p-values are two-sided, and a value of < 0.05 is considered statistically significant.

We used the SPSS version 24.0 for Windows (IBM Corp, Armonk, NY), and GraphPad Prism 9.3 software (GraphPad Software, La Jolla, CA) for analysis.

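### The DDD endpoint is a per-patient average over drugs, so it measures dose per drug rather than total drug load and can move either way when a drug is stopped or added

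*Protocol article*

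**What the plan says.** All places are in the protocol article.

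- **Secondary objectives.** Two medication outcomes are named together: "the number of required AHDs as well as the defined daily dose (DDD) is calculated at t0 and t12 in both arms". The stated aim is to see whether the arms differ over time. No direction of change is given.
- **Statistical analysis, construction of the endpoint.** After defining the DDD as an average maintenance dose, the text says: "These averages are used to determine how many times the DDD for each individual drug is used". The next sentence reduces the per-drug multiples to one number per patient and visit: "Subsequently, the averages of these DDDs are calculated for t0 and t12 for individual patients". A sum or total is not mentioned anywhere in the article.
- **Statistical analysis, test.** "Differences in blood pressure and DDDs over time within the same arm are tested by means of a paired sample t-test". The comparison between arms is an independent-samples t-test.
- **Inclusion and exclusion criteria.** Patients enter on "at least three AHDs from different drug classes, including a diuretic, or at least four AHDs from different drug classes".
- **Standard of care (SoC) alone.** During follow-up "it is allowed to make changes to the AHD treatment during every visit, without restriction with regard to the choice or dose of drugs". The other arm receives its intervention on top of this same standard care.

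**The concern.** DDD multiples put different drugs on one scale so that they can be added into a single measure of how much medication a patient is on. Averaging them over the patient's drugs removes one of the two components of that load. The mean divides by the number of drugs, and treating physicians may change that number at any visit after randomisation, possibly to a different extent in the two arms. What remains is the typical dose intensity of whichever drugs the patient is still prescribed.

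The t-tests would be run on that quantity. If the arms differ at 12 months mainly because drugs were stopped in one or added in the other, the mean may show no difference, or a difference opposite in sign to the change in total medication. A reader told that mean DDD rose in one arm could take it as more medication when it was less.

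**Working it through.** **Inputs.** The definition, the tests and the freedom to change drugs come from the sections cited above. The protocol gives no DDD multiples and no expected change, standard deviation or power for this endpoint, so there is no planned figure to reproduce. All multiples below are assumptions chosen to show the behaviour of the two summaries.

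**Formulas.** Let a patient take k drugs with multiples x_1, ..., x_k, where x = daily dose / DDD, and let m be their mean.

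- Stopping drug j changes the mean by (m − x_j)/(k − 1) and the sum by −x_j.
- Adding a drug with multiple y changes the mean by (y − m)/(k + 1) and the sum by +y.

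So the sum always moves with the stop or addition. The mean moves according to where the drug lies relative to m.

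**Examples (assumed multiples).**

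| Change | Mean | Sum |
|---|---|---|
| 1, 1, 0.5: stop the 0.5 | 0.83 to 1.00 | 2.5 to 2.0 |
| four drugs at 1.0: cut to two | 1.00 to 1.00 | 4.0 to 2.0 |
| 2, 1, 1, 0.5: stop the 0.5 | 1.125 to 1.333 | 4.5 to 4.0 |
| 2, 1, 1, 0.5: stop the 2.0 | 1.125 to 0.833 | 4.5 to 2.5 |
| three drugs at 1.0: add one at 0.5 | 1.000 to 0.875 | 3.0 to 3.5 |
| 2, 2, 1, 1: doses cut to 1, 1, 1, 1, no stop | 1.50 to 1.00 | 6.0 to 4.0 |

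Formula check on the first row: (0.833 − 0.5)/2 = +0.167, giving 1.00. On the fourth row: (1.125 − 2)/3 = −0.292, giving 0.833.

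**Average behaviour.** If each of a patient's drugs is equally likely to be the one stopped, the expected change in the mean is (1/k) Σ (m − x_j)/(k − 1). This is exactly 0, because deviations from a mean sum to zero. A simulation agrees (3, 4 or 5 drugs; multiples drawn evenly from 0.5, 1, 1.5 and 2; one random drug stopped). The mean rose in 44–47% of patients, was unchanged in 6–13% and fell in 44–47%, with an average change of about 0.00. The sum fell every time, on average by 1.25 DDD, which is the average multiple: (0.5 + 1 + 1.5 + 2)/4 = 1.25.

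**Does the drug count fill the gap?** Take four drugs at 0.5 replaced by two at 1.0. The count goes from 4 to 2 (down 50%), the mean from 0.5 to 1.0 (up 100%), and the sum from 4 × 0.5 = 2.0 to 2 × 1.0 = 2.0. The two planned outcomes point in opposite directions while total load is unchanged.

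**The case against.** **A stronger reading does not hold.** A reader might infer that stopping a drug always leaves the average unchanged or raises it, so that the endpoint cannot show a lower drug load. That goes too far. Stopping a drug with an above-average multiple lowers the mean (1.125 to 0.833 above), and in the simulation falls were about as frequent as rises. Dose reductions without a stop also lower it (1.50 to 1.00), and the protocol allows changes in dose as well as in choice of drug.

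**The count records stops.** The number of AHDs is a separate secondary outcome, and within one patient count × mean = sum over the same drugs. This stands for individual patients: nothing is lost from the data. It does not carry over to arm-level averages. Two patients, one on four drugs at 0.5 and one on two at 1.0, have average count 3 and average mean DDD 0.75, with product 2.25, but their average sum is 2.0. Comparing each component separately between arms is not a comparison of total load.

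**No direction is stated.** A reader might also infer that the protocol aims to show less medication in the intervention arm. It asks only whether the arms differ over time, and it does not name total load as the target of the DDD outcome. A deliberate choice of dose intensity as a complement to the count would be coherent, but the article does not say that this is what is meant.

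**The wording may mean something else,** such as group averages of patient totals. The phrase about individual patients makes the within-patient mean the natural reading. If totals were intended, the same edit is needed.

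**The examples are illustrations.** They show that divergence is possible and in which direction. They do not show how large it will be in this trial.

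**Conclusion.** The point holds in a limited form. As written, the DDD endpoint is the mean dose intensity per drug. When a drug is stopped or added it can rise, fall or stay unchanged, so it is not a reliable measure of how required medication changes between arms. The drug count compensates only in part, because it ignores dose.

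The size in this trial cannot be stated. In assumed cases the gap runs from a mean up 20% with a sum down 20% (0.83 to 1.00 against 2.5 to 2.0) to no change in the mean with a sum down 50%. If the drug stopped is a random one of the patient's drugs, the expected change in the mean is zero whatever the multiples. That last result needs only the equal-chance assumption; the percentages depend on the assumed multiples.

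Severity is moderate. One secondary endpoint is affected, the data needed for the better summary are the same, and the primary analysis and sample size are untouched.

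**What to change.** In the Statistical analysis section, replace the averaging sentence with a definition of total DDD: for each patient, the sum over all prescribed AHDs of daily dose divided by that drug's DDD, at t0 and at t12. Compare this sum between arms and report it beside the AHD count. Keep the mean DDD per drug as a descriptive figure only. If dose intensity per drug was the intended target, say so in Secondary objectives and still report the sum.

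The cost is one sentence. No extra data are needed, since the sum uses the same doses and DDD values as the average, and neither visits nor sample size change. The edit should be made before any DDD results are analysed, so that the choice of summary cannot be seen to depend on them.

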### Methods of measurement

#### Blood pressure measurement

24-h blood pressure is recorded with the available ABPM device on site. All devices have to be approved for use in clinical practice. Measurements are performed with the device attached to the non-dominant arm if possible. Patients are instructed to relax their arm during the measurements and to pursue their normal daily activities. During the 24-ABPM patients are also asked to write down physical and stressful activities in a diary, as well as their true sleeping times. Depending on the hospital, BP is measured at a 20-min or 30-min interval during daytime and a 30-min or 60-min interval at night-time. Measurements are included if > 50% of the 24-h measurements was successful which includes at least 20 valid awake measurements and 7 valid asleep measurements [28, 29]. If a patient is eligible for the study because of a 24-h ABPM ≥ 135 and/or 85 mmHg measured for clinical purposes and the fingerprick is obtained within 4 weeks after this measurement, it is a allowed to use this ABPM measurement as inclusion criterion. However, an AOBP has to be performed at time of the fingerprick and needs to be ≥ 140 and/or 90 mmHg. If a patient does not want to do a 24-ABPM during the eligibility visit, they are excluded from participation. At all the follow-up visits, the 24-h ABPM can be replaced with a 30-min AOBP upon reasonable request of the patient as stated before.

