## Discussion

This will be the first trial that focusses specifically on patients with RH and combines measurement of drug concentrations to identify non-adherence to AHDs, with a comprehensive feedback to the patients to improve non-adherence. Measurement of drug concentrations is not hampered by the availability of places for phlebotomy, as DBS sampling can be performed by anyone at any time with the right training and materials. Also, patients are selected based on their blood pressure and number of prescribed AHDs instead of based on the adherence estimation of physicians. Hereby, including patients that otherwise would not be recognized as being non-adherent. Lastly, if this trial shows positive outcomes for the intervention it can be directly implemented in clinical practice, which would be a great improvement in the treatment of RH.

However, there are some possible problems that can occur due to the study design. First, patients are obliged to do a 24-h ABPM to eliminate white coat hypertension. This blood pressure measuring method is the most reliable to establish true hypertension, but not patient friendly, as it often interferes with planned daily activities and the ability to sleep [37, 38]. Therefore, this could lead to the exclusion of a specific group of patients that potentially do not have true resistant hypertension [39]. We tried to make the trial as patient friendly as possible, to include, preferably, daytime measurements or AOBP as alternatives for the 24-ABPM if a patient tends to drop-out because of the ABPM.

Second, not all AHDs could be included in the UPLC-MS/MS method since extensive validation is necessary before use in clinical practice [25]. For inclusion patients have to use at least two AHDs that can be measured with our method, but it is not obliged to only use AHDs that can be measured. As a result, there is a considerable chance that we are not able to measure all used antihypertensive drugs, and potentially miss non-adherence to certain AHDs. However, the importance of adherence will be mentioned during feedback conversations thereby improving non-adherence to AHDs we are not able to measure.

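### The blood-pressure t-tests do not hold the measurement method constant: ABPM is required at t0, AOBP may replace it at follow-up, and the change score then includes a method difference

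*Protocol article*

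**What the plan says.** **At t0.** The protocol article, Blood pressure measurement, makes ABPM a condition of entry: "If a patient does not want to do a 24-ABPM during the eligibility visit, they are excluded from participation". Patients who enter on an ABPM taken for clinical purposes, with the fingerprick within 4 weeks after it, must also have an office reading: "an AOBP has to be performed at time of the fingerprick and needs to be ≥ 140 and/or 90 mmHg". They are the only patients for whom an AOBP at t0 is required.

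**At follow-up.** The same section says: "At all the follow-up visits, the 24-h ABPM can be replaced with a 30-min AOBP upon reasonable request of the patient as stated before". Standard of care (SoC) alone describes the t3, t6 and t12 visits as "with preferably a 24-h ABPM, and otherwise an automated office blood pressure (AOBP) combined with DBS sampling". The intervention is added to SoC, so this applies to both arms. The Discussion gives a wider list: "daytime measurements or AOBP as alternatives for the 24-ABPM if a patient tends to drop-out because of the ABPM".

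**Analysis.** Statistical analysis says: "Differences in blood pressure and DDDs over time within the same arm are tested by means of a paired sample t-test", with an independent-samples t-test between arms. It names no blood-pressure variable, same-method restriction or analysis by method. The intention-to-treat set is all randomised patients. The per-protocol set needs measurements at t0, t12 and one of t3 and t6, by whatever method.

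**Scales.** Inclusion and exclusion criteria uses 135/85 mmHg for daytime ABPM and 140/90 mmHg for office readings. The AOBP rule at entry also uses 140/90.

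**The concern.** For most patients the only t0 value is an ABPM. If such a patient has AOBP at t12, either the change score crosses methods or the patient leaves the test. The article states no exclusion, so the plan followed as written gives cross-method differences. Its cut-offs, 5 mmHg apart, show that it does not treat the two methods as interchangeable.

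A yes/no classification of resistant hypertension can apply a separate cut-off to each method. A mean change has no such device, so a patient whose pressure is unchanged shows a change equal to the method difference. The within-arm tests could then report a change that is partly or wholly due to method. The between-arm test is exposed if patients in one arm ask for AOBP more often. That is possible, because the request comes after randomisation and is meant for patients inclined to drop out.

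**Working it through.** **1. The plan's own sample size.** From Sample size calculation: prevalence 80% v 90%, two-sided 0.05, power 80%. The unpooled formula gives

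n = (1.960 + 0.842)² × (0.9×0.1 + 0.8×0.2) / 0.10² = 196.2,

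which reproduces the stated 196 per arm. That figure is not in dispute; it is used below as the number analysed.

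**2. Inputs not in the document (assumptions).**
- Method offset d = 5 mmHg, taken from 140 − 135 (and 90 − 85).
- SD of within-patient change: 15 mmHg, range 12 to 20.
- AOBP share at t12: 10%, 20% or 30%.

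**3. Within-arm paired test, no true change.** With AOBP share f,

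shift = f × d; SE = √[(SD² + f(1−f)d²) / 196].

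At f = 0.20 and SD 15: shift = 0.20 × 5 = 1.0 mmHg; SE = √[(225 + 0.16×25)/196] = √(229/196) = 1.08. Two-sided rejection under the normal approximation is 1 − Φ(1.96 − 1.0/1.08) + Φ(−1.96 − 1.0/1.08) = 15%.

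| AOBP share | Shift (mmHg) | Rejection, SD 15 | SD 20 to SD 12 |
|---|---|---|---|
| 10% | 0.5 | 7.5% | 6% to 9% |
| 20% | 1.0 | 15% | 11% to 21% |
| 30% | 1.5 | 28% | 18% to 40% |

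The nominal level is 5%. No imbalance between arms is needed.

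**4. Between-arm test, no true difference.** With shares f₁ and f₀,

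bias = (f₁ − f₀) × d; SE = √{[2·SD² + (f₁(1−f₁) + f₀(1−f₀))d²] / 196}, about 1.53 at SD 15.

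| Shares | Bias (mmHg) | Rejection, SD 15 | SD 20 to SD 12 |
|---|---|---|---|
| 20% v 20% | 0 | 5.0% | 5% |
| 25% v 20% | 0.25 | 5.3% | 5.2% to 5.5% |
| 30% v 20% | 0.5 | 6.2% | 6% to 7% |
| 40% v 20% | 1.0 | 10.0% | 8% to 13% |

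**5. Sensitivity to the offset.** Both biases are proportional to d, take its sign, and vanish at d = 0. Halving d to 2.5 mmHg, with SD 15, gives a within-arm shift of 0.5 mmHg and 7.5% rejection at 20% AOBP. Between arms, a 20-point gap then gives 0.5 mmHg and 6.3%.

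**The case against.** **The article never tells anyone to subtract an ABPM from an AOBP.** It says only that differences in blood pressure are tested, and the exact variable could sit in a full protocol or SAP that is not shown. This stands in part: the mixed pairing and the word daytime are inferred. But the article fixes both the tests and the measurement scheme, and the two do not fit. A 24-h mean at t0 would cross methods in the same way. A later document can choose the variable, but it cannot supply a t0 AOBP for patients who never had one.

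**The randomised comparison is largely protected.** This stands for equal AOBP use: a common shift cancels between arms. A reader might infer that the treatment comparison is generally biased, with type I error near 10%. The document does not support that. The 10% figure needs a 20-point gap. AOBP is a fallback granted on reasonable request, and participants have already accepted one ABPM. A 10-point gap gives about 6%.

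**The offset is not a measurement.** This stands. A gap between diagnostic cut-offs is not a mean difference between a 30-minute AOBP and a daytime ABPM in these patients. The article gives no offset, AOBP share or SD.

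**Mean blood pressure is not a listed endpoint.** This stands. The objectives list resistant hypertension, adherence, number of drugs, DDD and cost-utility. A reader might extend this point to the primary endpoint, but resistant hypertension is classified with a cut-off for each method, and this calculation does not bear on it.

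**Imputing ABPM from AOBP, or adding a method covariate, would be a weak repair.** This stands. At follow-up AOBP replaces ABPM, so concurrent pairs are not produced there. The only overlap the article requires is the t0 subset with a clinical ABPM up to 4 weeks earlier. Method is also chosen after randomisation, so adjusting for it can introduce selection bias.

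**Conclusion.** The point holds, within limits. As written, the blood-pressure tests combine an ABPM at t0 with an AOBP at t12 for any patient who switches, and nothing in the stated analysis removes the difference. The clear damage is to the within-arm paired tests, where a 20% switch is enough to triple the nominal error rate under the assumed 5 mmHg offset and 15 mmHg SD. The between-arm test is affected only through unequal AOBP use, and modestly unless the gap is large. The direction is unknown in advance.

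The structural conflict follows from the text. Its size rests on the assumed offset, SD and AOBP shares and would shrink with a smaller offset. It deserves correction because the repair is simple, but it concerns a supporting analysis and does not undermine the primary endpoint or the sample size.

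**What to change.** **Statistical analysis section.**
- Define the blood-pressure variable for the t-tests as daytime mean ABPM, and state that AOBP is not subtracted from ABPM.
- Treat a visit with AOBP only as missing daytime ABPM, handled by a missing-data model that uses t0 daytime ABPM, daytime ABPM from other visits, and arm.
- Report the AOBP share by arm at each follow-up visit, with a sensitivity analysis that includes the AOBP values.
- Do not make imputation from AOBP, or a method covariate, the main analysis.

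**Measurement sections.** Reconcile Standard of care (SoC) alone and Blood pressure measurement, which offer only AOBP as the substitute, with the Discussion, which also names daytime measurement. If a daytime-only ABPM is accepted, the validity rule in Blood pressure measurement, which requires 7 valid asleep readings, must be worded so that it does not exclude such a recording.

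**Cost.** A few sentences and one missing-data model, with no new visit or device. Intervals will be somewhat wider, because AOBP-only visits no longer count as observed values.
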